
### 2.9. Statistical Analysis

#### 2.9.1. Primary Analyses

Each composite score (acceptability, trust, perceived risk) will be analyzed by a mixed repeated-measures ANOVA, with autonomy level (four scenarios) as the within-subjects factor and presentation sequence (four Williams sequences) as the between-subjects factor. The Greenhouse–Geisser correction will be applied when Mauchly’s test indicates a sphericity violation (Huynh–Feldt for ε between 0.75 and 1), and the multivariate approach (Pillai’s criterion) will be reported in parallel as a sphericity-robust check. H1 and H2 will be tested with within-subjects trend contrasts across the autonomy gradient. Because acceptance need not fall in a straight line, the complete set of orthogonal polynomial contrasts—linear, quadratic, and cubic—is pre-specified, and each is reported together with the proportion of the omnibus effect it accounts for. A purely linear profile leaves the quadratic and cubic components negligible, whereas a step between two adjacent levels appears as a large linear component accompanied by a substantial quadratic or cubic one. Because every monotone step is linear-dominant, the polynomial decomposition establishes departure from a straight line but cannot by itself locate the break; the break is identified only from the Holm-corrected adjacent-pair contrasts (A–B, B–C, C–D). A quadratic-dominant profile with a small linear component would instead indicate a non-monotone pattern, which the hypotheses do not predict and which would be reported as such. A non-monotonic or threshold pattern will be reported as such rather than summarized by the linear trend alone. Post hoc comparisons use dependent-samples *t*-tests for the six scenario pairs with Holm’s sequential correction, applied within each hypothesis-defined family of tests in line with current guidance on multiplicity control [74]. Effect sizes will be reported as partial η^2^ for omnibus tests and Cohen’s dz for pairwise comparisons, with 95% confidence intervals, following effect-size-centered reporting recommendations [64]. Assumption checks include graphical inspection of difference-score distributions; as a distributional robustness analysis, the Friedman test with Holm-corrected Wilcoxon signed-rank pairwise comparisons will be reported alongside each primary test—supplemented by ordinal (cumulative-link) models as sensitivity analyses for the Likert-based outcomes [71]—and the concordance of parametric and nonparametric conclusions stated explicitly. Order dependence is tested directly as the scenario × sequence interaction; a non-significant interaction, together with equivalence of the four sequence-specific profiles, supports pooling across sequences. Independently of that test, the autonomy effect is re-estimated from a linear mixed model with random intercepts per participant and additive fixed effects of autonomy level and serial position (1–4). The Williams square renders this model identified, so the estimate is adjusted for arbitrary—not merely linear—serial-position and fatigue effects, while first-order carry-over is balanced by the design rather than modeled; position-adjusted and unadjusted estimates are reported side by side, and any material divergence between them is treated as evidence of an order artifact and interpreted accordingly. Perceived difficulty (DIF1) and perceived technical sophistication (MAN2) are each added as time-varying covariates in further sensitivity models, addressing fatigue and the possibility that responses track the apparent complexity of the system rather than its autonomy. Finally, between-person heterogeneity in response profiles is examined by adding a random slope for the linear autonomy contrast and testing the improvement in fit by a likelihood-ratio test; a substantial random-slope variance indicates that an average trajectory conceals distinct response patterns and licenses the exploratory typology described in Section 2.9.2. Because a non-significant test is not evidence of absence, a smallest effect size of interest of *dz* = 0.20—the value detectable at the Bonferroni bound for the six pairwise contrasts at *N* = 300—is fixed in advance, and equivalence testing by two one-sided tests against that bound is reported alongside every null pairwise result, so that any claim that two adjacent scenarios do not differ rests on an equivalence test rather than on the absence of significance.

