
#### 2.9.2. Secondary and Exploratory Analyses

(i) Moderation (H4): the scenario × AI familiarity (B1, centered) interaction, via repeated-measures ANCOVA or a linear mixed model with random intercepts per participant, the recommended framework for vignette data [62]; presentation sequence is retained as a between-subjects factor here, as in every repeated-measures model in this protocol. (ii) Person-level multiple regression: mean acceptability across scenarios predicted by AI familiarity, general AI attitudes, and demographics (reporting *B*, *SE*, β, 95% CI, R^2^, VIF). (iii) Responsibility migration (H3): a 4 × 4 mixed ANOVA (scenario × actor, RES1–RES4, both within-subjects; presentation sequence between-subjects) with Greenhouse–Geisser correction; the scenario × actor interaction is the direct test of H3. Because H3 is confirmatory, it receives the same order controls as H1 and H2: the sequence terms are inspected first, and the migration estimate is repeated in a linear mixed model containing an additive serial-position term. (iv) Responsibility concentration: a normalized Herfindahl–Hirschman index computed per scenario from the relative weights of the three responsible actors (surgeon, hospital, AI developer; RES4—unavoidable medical uncertainty—is not a responsible actor and is analyzed separately), compared across scenarios by mixed repeated-measures ANOVA with sequence as a between-subjects factor; low values index diffusion of responsibility across actors, operationalizing the “problem of many hands” described in the responsibility literature [44,45]. (v) RES5 (moral duty) and RES6 (outcome-independent accountability): mixed repeated-measures ANOVAs across scenarios with sequence as a between-subjects factor, Holm-corrected within the family. (vi) Global preference (P1): a goodness-of-fit chi-square with standardized residuals over six analysis categories on 5 degrees of freedom. The six categories are the four scenarios, “I would prefer AI not to be involved in any way,” and a combined “no clear preference” category; the last pools the item’s two undecided options (“I have no preference” and “I cannot decide”), which are combined a priori because neither expresses a preference between scenarios and each is expected to be sparse. Consistency between stated preference and each participant’s maximum-acceptability scenario is reported descriptively. (vii) Exploratory: P4a and P4b (the surgeon’s permanent legal and, separately, moral responsibility) analyzed descriptively, compared with each other by a dependent-samples test on the within-person difference, and correlated with RES5/RES6; free-text concerns (P2) summarized by brief thematic analysis. (viii) Sensitivity analyses: primary analyses repeated (a) excluding participants with a single attention-check failure (who are retained under the primary rule) and (b) excluding participants with any comprehension failure, to demonstrate that conclusions do not depend on the cleaning criteria [69]. (ix) Order effects: descriptive profiles by sequence, the scenario × sequence interaction with its effect size and 95% confidence interval, and sequence-specific manipulation-check profiles. (x) Response-pattern typology (exploratory): where the random-slope test of Section 2.9.1 indicates heterogeneity, individual acceptability trajectories across autonomy levels are classified by latent-class growth analysis, with class enumeration by BIC and entropy and a minimum class size of 5% fixed in advance, and class membership described against AI familiarity, healthcare-system trust, and demographics; no inferential claim is attached to this analysis. (xi) Healthcare-system trust (B6) enters the person-level regression of (ii) as a covariate and is examined as an exploratory moderator of the autonomy effect, alongside healthcare contact frequency (B5) and prior surgical experience (B4, B4a). (xii) Subgroup analyses, all of which are secondary or exploratory, are governed by a minimum-cell rule fixed in advance: inferential tests within a subgroup are reported only where that subgroup contains at least 50 valid participants, the size at which a within-subject difference in *dz* = 0.40 is detectable at power 0.80; subgroups of 30–49 are reported descriptively with 95% confidence intervals and labeled as underpowered; subgroups below 30 are pooled into a residual category or not reported. A difference between subgroups is never inferred from a significant effect in one and a non-significant effect in another; only the formal interaction term, with its own confidence interval, supports such a claim. The set of moderators is fixed a priori, in the pre-registration, to seven: AI familiarity (B1), healthcare-system trust (B6), healthcare contact frequency (B5), prior surgical experience (B4/B4a), education (D3), age (D2), and field of activity (D4). Results are reported for all seven irrespective of significance, and no further moderator is added after the data are seen. (xiii) Missing data: because all closed items are mandatory, missingness in the dependent variables is structurally impossible within a submitted questionnaire. Two other forms of missingness remain. The first is unit-level, from questionnaires abandoned before submission. The platform is configured not to store partial submissions, so responses from abandoned questionnaires are neither retained nor analyzed (Section 2.10 and Appendix A.1). Attrition is therefore characterized from the platform’s page-level counters—how many participants reached each page—rather than from partial response data, and is reported as drop-out by serial position in the participant-flow diagram. Analyses are accordingly restricted to complete cases, that is, participants with all four scenario blocks, and no imputation is performed: with no partial records retained, there are no incomplete cases to impute. The second is item-level, on the background and demographic items that offer a “prefer not to answer” option or, in the case of B4 and B4a, are not displayed where the explicit health-data consent is declined; these are treated as a distinct category descriptively and as missing in inferential models, with a sensitivity analysis retaining the category in the person-level regression. Because complete-case analysis is not neutral when attrition is differential, drop-out is compared across the four presentation sequences, and any imbalance is reported and carried into the interpretation of the order analyses. All tests are two-tailed at α = 0.05, with exact *p*-values, effect sizes, and 95% confidence intervals reported for all tests, including non-significant ones. On closed 1–7 scales, no distribution-based outlier removal is applied.

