## 3. Expected Results

Based on the algorithm-aversion and trust studies [19,37,38], we expect acceptability and trust to decline—and perceived risk to rise—across the autonomy gradient from Scenario A to Scenario D, with the largest drop anticipated at the transition to autonomous planning (Scenario D), where the surgeon’s corrective role is described as residual. Whether that decline is a gradient or a step is an open question that the design is equipped to address: a step would show as a substantial quadratic or cubic component alongside the linear one, and its location would be identified by the adjacent-pair contrasts, which we expect to place the largest single drop at C–D. Nor do we assume the pattern is homogeneous across participants; a substantial random-slope variance would itself be informative, indicating that an average trajectory conceals distinct groups of respondents rather than describing a shared response. The expectation of decline is, in any case, consistent with survey evidence that public comfort is conditional on physician supervision [24,25,31]. For responsibility attribution, we expect the surgeon to be assigned the dominant share in low-autonomy scenarios [41], with a progressive migration toward the AI developer—and possibly a diffusion of responsibility across actors, indexed by falling Herfindahl concentration—as autonomy increases [44,45]. We expect the manipulation check (perceived AI control) to order the scenarios from A to D within each of the four presentation sequences, validating the experimental gradient independently of serial position, and we expect no scenario × sequence interaction. Should one nevertheless appear, the position-adjusted mixed-model estimate becomes the primary basis for interpreting H1–H3, and the magnitude of the order effect will itself be reported as a finding about the stability of vignette-based autonomy judgments. Given the design’s sensitivity (power of 0.99 against small within-subjects effects at ρ = 0.50, and 0.95 at ρ = 0.30, for the target sample), a null result for a primary hypothesis would place a tight upper bound on the size of any autonomy effect rather than leaving the question open; the pre-specified equivalence tests of Section 2.9.1 make that bound explicit rather than infer absence from non-significance [70]. The moderation hypothesis (H4) is powered only for medium-small interactions and will be interpreted with corresponding caution. Results will inform the ordering of public concerns along the assistance-to-autonomy continuum and identify which implementation configurations are publicly acceptable entry points for surgical AI in Romania.

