H4. moderation by AI familiarity (partially exploratory)	RM-ANCOVA or linear mixed model with random intercepts: scenario (within) × B1 (centered), sequence between	F (or likelihood-ratio test), *p*, *f*^2^; simple slopes with 95% CI
Global preference (P1)	Goodness-of-fit chi-square over 6 analysis categories (2 undecided options pooled); standardized residuals; consistency with maximum-acceptability scenario, descriptive	χ^2^, *df*, *p*, *w*; standardized residuals
Predictors of acceptability	Person-level multiple regression: mean acceptability on familiarity, general attitudes, demographics	*B*, *SE*, β, 95% CI, R^2^, VIF
P2, P4a/P4b (exploratory)	Brief thematic analysis (P2); descriptive statistics, within-person P4a–P4b difference, and correlations with RES5/RES6	Theme frequencies; Pearson/Spearman *r*
Order dependence (design validation)	Scenario × sequence interaction in the mixed RM-ANOVA; position-adjusted linear mixed model (autonomy + serial position, random intercepts)	*F*, corrected *df*, *p*, partial η^2^ (90% CI); adjusted vs. unadjusted scenario means
Functional form of the autonomy effect	Orthogonal polynomial contrasts (linear, quadratic, cubic); Holm-corrected adjacent-pair contrasts	*F*, *p*, partial η^2^ per contrast; share of the omnibus effect
Autonomy vs. technical complexity	Mixed RM-ANOVA on MAN2 (sequence between); primary models re-estimated with MAN2 as a time-varying covariate	*F*, corrected *df*, *p*, partial η^2^; adjusted scenario means
Between-person heterogeneity (exploratory)	Random-slope linear mixed model; latent-class growth analysis of individual trajectories	Likelihood-ratio χ^2^, *p*; random-slope SD; class sizes, BIC, entropy

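### The H4 and position-adjusted mixed models have random intercepts only, so their linear-trend and A–D inference is anti-conservative if autonomy slopes vary between people

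*Protocol article*

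**What the plan says.** The protocol article states the random-effects structure of two inferential mixed models.

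- **H4.** Section 2.9.2(i) tests the scenario × B1 interaction "via repeated-measures ANCOVA or a linear mixed model with random intercepts per participant". Table 5 repeats it: "RM-ANCOVA or linear mixed model with random intercepts: scenario (within) × B1 (centered), sequence between". Table 5 also promises simple slopes with 95% intervals.
- **Position-adjusted autonomy effect.** Section 2.9.1 re-estimates it from "a linear mixed model with random intercepts per participant and additive fixed effects of autonomy level and serial position", and Table 5 lists the same structure. Section 3 adds that, if a scenario × sequence interaction appears, "the position-adjusted mixed-model estimate becomes the primary basis for interpreting H1–H3".

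A random slope for the linear autonomy contrast is mentioned once as a modelling step, in Section 2.9.1. It is added to assess heterogeneity by a likelihood-ratio test, and a substantial slope variance "licenses the exploratory typology described in Section 2.9.2". Section 3 says of the response pattern: "Nor do we assume the pattern is homogeneous across participants". No sentence carries the slope into the models used to test H1, H2 or H4. For H3, Section 2.9.2(iii) announces a mixed model with a serial-position term but does not state its random effects.

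**The concern.** A random intercept alone imposes compound symmetry: every within-person contrast is judged against one pooled error. If people differ in how steeply acceptance falls across A to D, contrasts that span the gradient vary more than that pooled error allows.

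The RM-ANOVA is protected by the Greenhouse–Geisser or Huynh–Feldt correction, with Pillai's criterion in parallel. The mixed models have no counterpart. The plan could therefore find substantial slope variance and still report intervals from a model that sets it to zero. Two places are exposed: the slope-type results that carry the directional claim of H4 (a smaller decline among people familiar with AI), and trend or A–D inference for H1 and H2 once the fallback is triggered.

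**Working it through.** **The plan's own figures.** For the four-level within factor, λ = f²·N·m/(1−ρ) with df 3 and 3(N−1). At f = 0.10, N = 300, m = 4, ρ = 0.50, λ = 0.01·300·4/0.5 = 24 and power is 0.991 (stated 0.99). The minimum N of 138 reproduces. For H4, u = 3 and λ = f²·N give a minimum detectable f² of 0.0368 (stated 0.037). The planning arithmetic is correct.

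**Inputs.** N = 300, four levels, two-sided α = 0.05 and complete cases are from the document. The slope SD is not in the document. I assume τ = 0.3, 0.5 and 0.7 per autonomy step, with residual SD σ = 1 and intercept SD 1. The mean inter-scenario correlation is then 0.46, 0.39 and 0.32, inside the plan's 0.30–0.50 range, so the pilot check on ρ would not flag it. Zero slope variance fits that range equally well, so the range is no evidence for these values.

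**Variances.** Code the levels −1.5, −0.5, 0.5, 1.5 (sum of squares 5). In complete balanced data the random-intercept model uses the pooled error σ² + 5τ²/3 for every normalised within-person contrast.

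| Contrast | True variance | Variance the model assumes |
|---|---|---|
| Linear trend (normalised) | σ² + 5τ² | σ² + 5τ²/3 |
| A − D | 2σ² + 9τ² | 2σ² + 10τ²/3 |
| Adjacent pair | 2σ² + τ² | 2σ² + 10τ²/3 |

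With R = true/assumed, actual type I error is 2[1 − Φ(1.96/√R)] and coverage is one minus that.

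| τ (τ²) | Linear: R, type I error | A–D: R, coverage | Adjacent: R, coverage |
|---|---|---|---|
| 0 (0) | 1, 0.050 | 1, 0.950 | 1, 0.950 |
| 0.3 (0.09) | 1.45/1.15 = 1.26, 0.081 | 2.81/2.30 = 1.22, 0.924 | 2.09/2.30 = 0.91, 0.960 |
| 0.5 (0.25) | 2.25/1.417 = 1.59, 0.120 | 4.25/2.833 = 1.50, 0.891 | 2.25/2.833 = 0.79, 0.972 |
| 0.7 (0.49) | 3.45/1.817 = 1.90, 0.155 | 6.41/3.633 = 1.76, 0.860 | 2.49/3.633 = 0.69, 0.982 |

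**Simulation at N = 300, same slope SDs.**

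- Linear trend: type I error 0.08 / 0.12 / 0.15.
- Linear × B1: 0.07 / 0.11 / 0.16.
- A–D coverage: 0.92 / 0.89 / 0.86.
- 3-df scenario × B1, the test named for H4: 0.047 / 0.050 / 0.064 in one set of runs and 0.056 / 0.057 / 0.068 in another.
- With each contrast's own error term, type I error for the linear trend and linear × B1 is 0.047–0.052.

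The 3-df test barely moves because the pooled error is right on average over the three contrasts: too small for the linear one, too large for the other two.

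**The case against.** The strongest reply is that the planned tests are mostly not the ones that inflate.

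- **H4 is the 3-df interaction** (df = 3 in Table 2), is labelled partially exploratory, and may be run as RM-ANCOVA instead. This stands: a reader might infer that the H4 p-value is badly inflated, but the named test stays near 0.05–0.07. What remains is the simple slopes in Table 5 and any linear × B1 reading used to support the direction of H4.
- **The default H1/H2 analysis is protected.** Its omnibus test has the sphericity correction, and the six paired t-tests each use their own error. This stands too. A reader might infer that the confirmatory results for H1–H3 rest on the faulty structure; they do so only if the fallback is triggered, which the plan does not expect. Even then the scenario means are not biased; only their standard errors are affected. For H3 the structure is simply unstated.
- **The plan does not say it expects slope heterogeneity.** Correct. It declines to assume homogeneity and tests it, so the inflation is conditional and its size rests on assumed SDs. At 0.7 per step the A-to-D change has a between-person SD of 3 × 0.7 = 2.1 points if residual SD is one scale point, which is large on a 1–7 scale. If heterogeneity is confined to Scenario D, inflation is milder (A–D main effect 0.058–0.089 for step-variance ratios of 0.25–2).
- **It is a detail for the SAP.** This does not stand: the article itself fixes random intercepts, in two sections and in Table 5.

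**Conclusion.** The point holds in a limited form. The two mixed models are stated with random intercepts only, and the slope test has no consequence for inference. Under linear slope heterogeneity with assumed SDs of 0.3–0.7 per step (residual SD 1), gradient-spanning single-df tests run at about 0.07–0.16 instead of 0.05, and A–D intervals cover 0.92–0.86 instead of 0.95.

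The error also runs the other way. Adjacent-pair contrasts taken from the same model are conservative (coverage 0.960–0.982), and adjacent pairs are how the plan locates the break. With no slope variance there is no problem.

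This is a should-fix specification gap. The documents do not support reading it as a failure of the primary ANOVA, of the 3-df H4 test, or of the point estimates.

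**What to change.** Before pre-registration, amend Sections 2.9.1 and 2.9.2(i) and Table 5 so that the position-adjusted and H4 mixed models keep a by-participant random slope for the linear autonomy contrast regardless of the likelihood-ratio result. Alternatively, specify an unstructured 4×4 within-person covariance, which also covers heterogeneity that is not linear. State the same structure for the H3 position-adjusted model in Section 2.9.2(iii). The likelihood-ratio test can stay as the trigger for the typology.

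The cost is wording only: no added participants or data, and 300 complete cases readily support the ten covariance parameters of the unstructured option. The downside is wider intervals for the trend and A–D where slopes do vary. At the assumed SDs the factor is √R: √1.26 = 1.12 to √1.90 = 1.38 for the trend, and √1.22 = 1.11 to √1.76 = 1.33 for A–D. Where slopes do not vary, there is essentially no widening.

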### 1.6. Objectives and Hypotheses

The primary objective is to evaluate the attitudes of Romanian adults recruited online—acceptability, trust, risk perception, and responsibility attribution—toward four progressive scenarios of AI implementation in facial reconstructive surgery. The secondary objectives are (i) to analyze the moderating effect of AI familiarity on acceptability across autonomy levels; (ii) to investigate how responsibility attribution (surgeon, hospital, AI developer, unavoidable medical uncertainty) varies across scenarios; (iii) to explore the moral–legal distinction in responsibility attribution; (iv) to identify the preferred model of AI implementation in facial reconstructive surgery; and (v) to quantify the influence of presentation sequence on all primary outcomes and to estimate the autonomy effect adjusted for serial position.

Four hypotheses will be tested. H1. Acceptability and trust decrease significantly as the level of AI autonomy in the surgical decision increases. H2. Perceived risk increases as human control over the decision process decreases. H3. Responsibility attribution shifts progressively from the surgeon toward the AI developer as algorithmic autonomy increases. H4. Prior familiarity with AI moderates the relationship between implementation scenario and acceptability, such that participants familiar with AI show a smaller decline in acceptability for high-autonomy scenarios; H4 is treated as partially exploratory, given the power constraints described in Section 2.5. H1–H3 fix the expected direction but not the functional form: each is tested by an omnibus effect of autonomy level followed by the full set of orthogonal polynomial contrasts, so that threshold-like or otherwise non-monotonic patterns are detected rather than forced into a linear trajectory (Section 2.9.1). A design-validation hypothesis is tested alongside them, namely that responses do not depend on the sequence in which the scenarios were presented; it is evaluated as the scenario × sequence interaction, and a non-null result is treated as evidence of order dependence to be reported and adjusted for, not as a substantive finding about autonomy.

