Because everyday usage collapses several distinct notions into one, the instrument separates them explicitly, and the header shown to participants states the intended sense. RES1–RES3 measure agent-directed responsibility—how much of the responsibility for an error each party should bear—and appear, together with RES4, under a common header that states that responsibility may be shared and that each party is to be rated separately rather than as a share of a fixed total, so that both diffusion and concentration are expressible; the header also glosses responsibility as answering for the error and putting it right, expressly distinguishing it from being found at fault in court. RES4 is not an agent and captures the alternative attribution that an error reflects irreducible clinical uncertainty; it is analyzed separately and is excluded from the concentration index. RES5 isolates moral responsibility from legal fault by construction (“even if the surgeon were not legally at fault…”), and RES6 isolates accountability in its outcome-independent sense—whether answerability depends on how the operation turned out—which is precisely what separates accountability from outcome-based blame. Legal liability proper is not measured per scenario. It is asked once, globally, and separately from the ethical claim, as two items presented on the same page and scale: P4a, that the surgeon should always remain legally responsible for any surgical outcome, and P4b, that the surgeon should always remain ethically responsible for it. Keeping them apart matters because a single double-barreled item would force the two notions to move together and would conceal exactly the pattern the responsibility literature predicts—a surgeon held morally answerable for an outcome to which no legal fault attaches. Both are analyzed descriptively and against RES5 and RES6, and their difference within participants—the extent to which a respondent holds the surgeon morally but not legally answerable—is itself reported. They are not treated as within-scenario outcomes, because lay judgments of legal liability depend on doctrinal assumptions that a short vignette cannot supply and that vary with the respondent’s exposure to the legal system; treating such judgments as a repeated-measures outcome would attribute a precision to them that they do not have. The Romanian wording of these items avoids the terms “culpă” and “răspundere juridică” except where legal fault is explicitly intended, and the pilot cognitive interviews (Section 2.8) probe specifically whether participants read RES1–RES3 as moral answerability, as causal contribution, or as legal liability. If the interviews reveal systematic conflation, the header wording will be revised, and the items retested before pre-registration, and the change documented.

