Trust in the healthcare system	B6	Likert 1–7	Covariate/exploratory moderator
Manipulation check (technical sophistication)	MAN2, per scenario (×4)	Likert 1–7	Design validation/covariate
Presentation sequence	SEQ	4 categories	Between-subjects design factor
Serial position of scenario	POS	1–4	Covariate (order, fatigue)

Abbreviations: DV, dependent variable; ACC, acceptability items; TRU, trust items; RSK, perceived-risk items; RES, responsibility items; MAN1 and MAN2, manipulation-check items; DIF1, perceived-difficulty item; ATT1 and ATT2, attention checks; CC_A–CC_D, comprehension checks; B1–B6, background items; G1–G4, general-attitude items; P1–P4b, preference items; D1–D7, demographic items; SEQ, presentation sequence; POS, serial position of the scenario; H1–H4, hypotheses 1–4.

**Table 5 healthcare-14-03030-t005:** Hypothesis-by-hypothesis analysis plan.

Hypothesis/Objective	Planned Test	Reported Coefficients
Manipulation validation	Mixed RM-ANOVA on MAN1 (autonomy within × sequence between) + polynomial trend contrasts; the intended ordering A → D expected within every sequence	*F*, corrected *df*, *p*, partial η^2^; ε(GG)
H1. acceptability and trust decline with autonomy	Mixed RM-ANOVA per composite, sequence as between-subjects factor (Greenhouse–Geisser) + orthogonal polynomial trend contrasts (linear, quadratic, cubic); post hoc dependent *t*-tests, Holm correction	*F*, corrected *df*, *p*, partial η^2^ (90% CI); pairwise dz (95% CI)
H2. perceived risk increases with autonomy	Mixed RM-ANOVA (autonomy within × sequence between) + orthogonal polynomial trend contrasts; post hoc dependent *t*-tests, Holm correction	*F*, corrected *df*, *p*, partial η^2^; pairwise *dz*
H3. responsibility migrates surgeon → AI developer	4 × 4 mixed ANOVA (scenario × actor within, sequence between), Greenhouse–Geisser; the scenario × actor interaction is the test of H3; repeated with a serial-position term	*F*, corrected *df*, *p*, partial η^2^; ε(GG)
Responsibility concentration	Normalized Herfindahl–Hirschman index (RES1–RES3) per scenario, compared by mixed RM-ANOVA (sequence between)	Mean HHI per scenario; *F*, *p*, partial η^2^
Moral–legal distinction	Mixed RM-ANOVAs on RES5 and RES6 across scenarios (sequence between); Holm correction within family	*F*, corrected *df*, adjusted *p*, partial η^2^

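### The confirmatory test of H3 is an undirected four-item scenario × actor interaction, which cannot tell a surgeon-to-developer shift from movement in the hospital item, in RES4, or in the opposite direction

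*Protocol article*

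**What the plan says.** Section 1.6 states H3 as: "Responsibility attribution shifts progressively from the surgeon toward the AI developer as algorithmic autonomy increases". The same section says that H1–H3 fix direction but not functional form, and that each is followed by the full set of polynomial contrasts. Sections 2.9.2(iii) and 2.12 label H3 confirmatory.

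The model in Section 2.9.2(iii) is "a 4 × 4 mixed ANOVA (scenario × actor, RES1–RES4, both within-subjects; presentation sequence between-subjects", and "the scenario × actor interaction is the direct test of H3". The H3 row of Table 5 repeats it: "the scenario × actor interaction is the test of H3; repeated with a serial-position term". The quantities to be reported there are F, corrected df, p, partial η² and ε. The row names no developer-minus-surgeon contrast, polynomial contrast or sign condition.

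On RES4, Section 2.6 says "RES4 is not an agent and captures the alternative attribution that an error reflects irreducible clinical uncertainty" and "it is analyzed separately and is excluded from the concentration index". Section 2.9.2(iv), directly after the H3 item, says that RES4 "is not a responsible actor and is analyzed separately".

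**The concern.** The hypothesis names two actors and a direction. The test asks only whether any of four rating profiles differs in shape from any other. Three patterns that are not H3 would make it significant:

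- only the hospital rating moves;
- only the unavoidable-uncertainty rating moves;
- the surgeon gains responsibility and the developer loses it.

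The response format adds to the problem. Section 2.6 has each party rated separately and not as a share of a fixed total, so a rise for one party implies no fall for another. Section 3 itself lists diffusion across actors as a possible result alongside migration. The omnibus interaction does not separate the two.

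What is at stake is one of three confirmatory conclusions. The statistic called the direct test of migration can be significant when there is no migration. Section 2.12 also bars applying a confirmatory label afterwards to an analysis that was not pre-registered, so a surgeon–developer contrast added once data are in could not carry H3.

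**Working it through.** **1. The plan's own figure.** Section 2.5 gives N = 138 for f = 0.10, ρ = 0.50 and four levels. With λ = f²·N·m/(1−ρ) = 0.01 × 138 × 4 / 0.50 = 11.04 on (3, 411) df, power is 0.801; at N = 137 it is 0.798. The figure reproduces. The article gives no power or detectable effect for the H3 interaction.

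**2. Degrees of freedom.** Four scenarios by four items gives 3 × 3 = 9.

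**3. Significance without migration.** The article gives no variances for the RES items, so these are assumptions: total variance 1, split into person 0.2, person × actor 0.3 and residual 0.5. Only the residual enters the interaction error.

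- *One item moves 0.10 SD per step; surgeon and developer are flat.* Scenario deviations are 0.10 × (−1.5, −0.5, 0.5, 1.5), with sum of squares 0.05. Removing the scenario mean over four items leaves 0.05 × (1 − 1/4) = 0.0375. Then λ = 300 × 0.0375 / 0.5 = 22.5, and power on (9, 2664) df is 0.94. The result is the same for the hospital item and for RES4.
- *Range.* With residual variance 0.3, λ = 37.5 and power is above 0.99. With 0.7, λ = 16.1 and power is 0.81. At N = 140 with 0.5, λ = 10.5 and power is 0.59.
- *Opposite shift: surgeon +0.10, developer −0.10 SD per step.* The sum of squares is 2 × 0.05 = 0.10, λ = 300 × 0.10 / 0.5 = 60, and power exceeds 0.999.

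A simulation under different assumptions agrees. It used item SD 1.5, variance shares of person 0.20, person × actor 0.35, person × scenario 0.10 and residual 0.35, the Greenhouse–Geisser correction, and N = 300:

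| True pattern, A to D | 9-df interaction, p < 0.05 | Positive linear trend in RES3−RES1, p < 0.05 |
|---|---|---|
| RES4 only, 0.3 points | 74% (67% if rounded to 1–7) | 2% |
| RES4 only, 0.5 points | over 99% | 2% |
| Hospital only, 0.5 points | about 100% | 2% |
| Surgeon +0.3, developer −0.3 | over 99% | 0% |

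Dropping RES4 alone (6 df) does not solve the problem: the hospital-only and opposite-direction cases remain significant in over 99% of runs.

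**4. Power when there is a migration.** For a shift lying wholly in one contrast of size dz, λ = N·dz², with error df = df × (N − 4). The benchmark dz = 0.20 is the smallest effect of interest in Section 2.9.1, which was set for pairwise scenario contrasts.

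| N, dz | λ | 1 df | 3 df | 6 df | 9 df |
|---|---|---|---|---|---|
| 300, 0.20 | 12.0 | 0.93 | 0.84 | 0.74 | 0.66 |
| 300, 0.25 | 18.75 | 0.99 | 0.97 | 0.92 | 0.88 |
| 300, 0.30 | 27.0 | 1.00 | 1.00 | 0.99 | 0.97 |
| 140, 0.20 | 5.6 | 0.65 | 0.48 | 0.37 | 0.31 |

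**5. Which focused test.** In the same simulation, a linear shift of 0.15 points each way gave power of 88% on 1 df, 74% on 3 df and 54% on 9 df. A step of 0.15 points each way at Scenario D gave 78%, 86% and 69%. The linear contrast is best for a straight line. The 3-df test on RES3−RES1 is better for a step, which is where Section 3 expects the largest drop in acceptance.

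**The case against.** Four replies have weight.

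*Nothing says that a significant interaction alone will be taken as support.* This is true. A reader might infer that the plan will declare migration whenever the interaction is significant. The documents do not say so: Section 1.6 fixes the direction, Section 2.9.2(iii) speaks of a migration estimate, and effect sizes with intervals are promised for all tests. The rejections in step 3 are also correct rejections of a real interaction, not type I errors. What stands is that the named test does not answer the named hypothesis and that no stated rule links them.

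*Follow-up contrasts are promised, and an analysis plan will be deposited.* Section 1.6 does promise polynomial contrasts for H1–H3. However, they are on autonomy level and do not isolate surgeon from developer. Section 2.9.1 applies trend contrasts to H1 and H2 only, and the H3 row of Table 5 has none. The article does not leave the H3 test open; it fixes it in two places.

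*RES4 belongs to a stated objective.* Secondary objective (ii) covers four loci, including unavoidable uncertainty, and the 4 × 4 model serves it. In Section 2.9.2(iv) the remark about separate analysis sits within the concentration-index definition. The statement in Section 2.6 is broader and does conflict with using RES4 as a level in the confirmatory test.

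*A purely linear replacement would be worse in some respects.* This is accepted. It would force the straight line that Section 1.6 declines to impose, and requiring both slopes to be significant would cost power.

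**Conclusion.** The point holds as a mismatch between hypothesis and test. That the interaction lacks direction and actor specificity follows from its definition and needs no simulation. Its size does depend on assumptions. At N = 300, slopes of 0.10 SD per step confined to the hospital item or to RES4 give significance in about 94% of trials (81% to over 99% across residual variances of 0.7 to 0.3), and an opposite shift gives nearly 100%.

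A reader might also infer that the interaction is generally underpowered. The figures do not support that. At dz = 0.20 its power is below the 0.80 target: 0.66 against 0.93 on 1 df at N = 300, and 0.31 against 0.65 at N = 140. By dz = 0.30 at N = 300 the loss is negligible. The status of RES4 and the missing polynomial contrasts for H3 are inconsistencies to reconcile whatever the variances.

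**What to change.** Change Section 2.9.2(iii) and the H3 row of Table 5 before pre-registration:

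- Make the confirmatory H3 test the scenario effect on the within-person difference RES3−RES1 (3 df, sequence in the model). Follow it with linear, quadratic and cubic contrasts, as for H1 and H2. Keep the planned repeat with a serial-position term.
- Count H3 as supported only if the linear trend in RES3−RES1 is positive.
- Report the separate RES1 and RES3 slopes with 95% confidence intervals, to show whether the surgeon falls, the developer rises, or both. Do not require each to be significant.
- Take RES4 out of the confirmatory actor factor and analyze it separately, as Section 2.6 states. Keep the four-locus interaction as descriptive support for secondary objective (ii).

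The cost is plan wording and a little more analysis, with no change to the instrument or sample. The omnibus interaction loses its confirmatory status. For a purely linear shift, the 3-df test gives up some power against a 1-df contrast (0.84 versus 0.93 at dz = 0.20 and N = 300) in return for sensitivity to a step.
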